### 2.5. Participant Timeline and Study Workflow

The schedule of enrolment, interventions, and assessments is systematised in Table 1. 

The study workflow, including data collection and management, is illustrated in Figure 1.

### 2.6. Recruitment (Patient and Provider)

A recruitment researcher (recruiter) will receive once monthly a database of admissions from the municipality Health Secretariat, including patients with a registered heart failure ICD-10 code (I11.0, I13.0, I42.0, I42. 6, I42.9, I50. 0, I50.1 or I50.9) who have been discharged during the previous month. Within one week, they will identify the primary care practice where the patient is registered, according to the patient’s address, in the public database *“Onde Ser Atendido”* [23] and invite the correspondent physician, who is responsible for the care of the patient, to participate in the study, by e-mail, telephone, or in person at the practice. When the physician accepts, the recruiter invites the patient by telephone or in person. We expect to invite all discharged patients from the municipality database (an average of 127 patients per month) and a 10% refusal rate, with an estimated recruitment rate of 114 patients/month, lasting for eight months, from March to September 2023. The recruitment will stop once the target sample size of 80 clusters with 10 patients each is reached.

The recruiter will obtain consent forms from patients and physicians, deliver orientation about the study process, and monitor the recruitment rate weekly. No financial incentive will be provided for the enrolment either of patients or physicians.

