## Abstract

Heart failure is a prevalent condition and a frequent cause of hospital readmissions and poor quality of life. Teleconsultation support from cardiologists to primary care physicians managing patients with heart failure may improve care, but the effect on patient-relevant outcomes is unclear. We aim to evaluate whether collaboration through a novel teleconsultation platform in the Brazilian Heart Insufficiency with Telemedicine (BRAHIT) project, tested on a previous feasibility study, can improve patient-relevant outcomes. We will conduct a parallel-group, two-arm, cluster-randomised superiority trial with a 1:1 allocation ratio, with primary care practices from Rio de Janeiro as clusters. Physicians from the intervention group practices will receive teleconsultation support from a cardiologist to assist patients discharged from hospitals after admission for heart failure. In contrast, physicians from the control group practices will perform usual care. We will include 10 patients per each of the 80 enrolled practices (n = 800). The primary outcome will be a composite of mortality and hospital admissions after six months. Secondary outcomes will be adverse events, symptoms frequency, quality of life, and primary care physicians’ compliance with treatment guidelines. We hypothesise that teleconsulting support will improve patient outcomes.

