#### 2.3.2. Inclusion Criteria for Study Centres and Staff

All 236 primary care practices from Rio de Janeiro municipality and their physicians are eligible for the study. According to the above criteria, we will include primary care practices progressively, determined by where the eligible patients are registered. 

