#### 2.7.3. Allocation—Implementation

An independent collaborator who does not participate in conducting the trial will receive the list of the practices to be stratified and randomised. After randomisation, they will send the recruiter an updated list containing allocation information. Based on the monthly report received from the Health Secretariat, the recruiter will allocate the patients in groups according to their registered practice. The researchers who are responsible for allocating and assigning interventions will not be involved in the intervention. Once one cluster reaches ten patients, the assignment for that cluster stops, in order to ensure equal cluster sizes.

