### 2.12. Study Duration

Based on the hospitals’ discharge frequency, we estimate recruiting patients for six months and collecting data for another six months after reaching the target sample and cluster size; therefore, the study will last one year.

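### The rule that stops recruitment at 80 practices with ten patients each is not attainable in the stated period under any plausible spread of patients, and the period itself is stated inconsistently

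*Protocol article*

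**What the plan says.** The target in the Abstract and section 2.6 is 80 practices with ten patients each, 800 in total, and section 2.6 makes it the stopping rule: "The recruitment will stop once the target sample size of 80 clusters with 10 patients each is reached". Section 2.7.3 treats ten as a size to be reached and not exceeded: "Once one cluster reaches ten patients, the assignment for that cluster stops, in order to ensure equal cluster sizes".

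The supply of patients is city-wide. Section 2.6 states "We expect to invite all discharged patients from the municipality database", gives "an average of 127 patients per month", and after 10% refusal continues "with an estimated recruitment rate of 114 patients/month, lasting for eight months, from March to September 2023". Section 2.3.2 adds "All 236 primary care practices from Rio de Janeiro municipality and their physicians are eligible for the study", with practices entering as their patients appear in the discharge reports.

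Section 2.12 gives another duration: "we estimate recruiting patients for six months and collecting data for another six months", making a one-year study.

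The article does not restrict invitations to 80 practices or select large ones. It does not say what happens to practices that never reach ten.

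**The concern.** The monthly rate agrees with the target only as a total: 114 × 8 = 912, which exceeds 800. The rule, however, is set per practice, and the article does not compare the inflow per practice with ten.

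If most practices cannot reach ten in the planned time, two courses remain. Recruitment overruns the one-year study by a wide margin, or someone decides during the trial when to stop and which partly filled practices count. The article has no rule for that decision. The clusters obtained would also differ from those behind the sample size in section 2.11.1, which assumes ten patients in every cluster.

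**Working it through.** **Inputs.** 127 patients a month, 10% refusal, 80 × 10 target (section 2.6); 236 practices (section 2.3.2); ICC 0.05, 40.1% event proportion, 30% effect, 72 clusters of ten (section 2.11.1). The between-practice CV is my assumption, because the article gives no distribution.

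**1. The plan's own figures.** 127 × 0.90 = 114.3, stated as 114. For 40.1% against 40.1% × 0.70 = 28.1%, two-sided 5% and 80% power, the usual two-proportion formula gives 243 per arm. The design effect is 1 + (10 − 1) × 0.05 = 1.45. Then 243 × 1.45 = 352.4 per arm, or 36 clusters per arm and 72 in all. Both figures reproduce.

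**2. Inflow per practice.** 912 / 236 = 3.86 in eight months. Leaving out about 12 feasibility-test practices gives 912 / 224 = 4.07. If only 80 average practices were open, they would yield 912 × 80 / 236 = 309 patients. Filling 80 × 10 needs 800 / 912 = 88% of all recruits to come from 80 / 236 = 34% of practices.

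**3. Practices reaching ten.** Let X be a practice's count after t months, with mean 114t / 236. X is Poisson if practices have equal rates (CV 0), and otherwise negative binomial with shape 1 / CV². The expected number of practices reaching ten is 236 × P(X ≥ 10).

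| CV (assumed) | Practices with ten at 8 months | Months until 80 are expected |
|---|---|---|
| 0 | 1.5 | 17.5 |
| 0.5 | 9.5 | 17.0 |
| 0.8 | 18.8 | 17.4 |
| 1.0 | 23.6 | 18.1 |
| 1.5 | 29.6 | 22.7 |
| 2.0 | 30.1 | 34.3 |

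The maximum over the CV is about 30 (near CV 1.8). As an extreme outside this model, suppose all 912 patients came from exactly 80 equally busy practices (mean 11.4). Poisson variation alone would leave 80 × P(X ≥ 10) ≈ 56 filled.

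**4. Stated periods.** March to September is seven calendar months. 114 × 6 = 684, 114 × 7 = 798 and 114 × 8 = 912. Only eight months passes 800, even as a total.

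**5. Stopping on the total with a maximum of ten.** Expected enrolment at t months is 236 × E[min(X, 10)], which I set to 800. Mean m and size CV s are taken over practices with at least one patient. Design effect = 1 + ((1 + s²)m − 1) × 0.05.

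| CV (assumed) | Months to 800 | Practices | m | s | Design effect | 800 / design effect | Power, 40.1% vs 28.1% |
|---|---|---|---|---|---|---|---|
| 0 | 7.02 | 228 | 3.5 | 0.50 | 1.17 | 684 | 92% |
| 0.5 | 7.08 | 216 | 3.7 | 0.62 | 1.21 | 664 | 91% |
| 0.8 | 7.36 | 199 | 4.0 | 0.68 | 1.25 | 643 | 90% |
| 1.0 | 7.74 | 186 | 4.3 | 0.70 | 1.27 | 630 | 89% |

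For 80 × 10, the effective size is 800 / 1.45 = 552 and the power 85%. At CV 1.5 and 2.0 the time to 800 rises to about 9.8 and 14.8 months.

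**The case against.** The strongest reply is that nothing here is strictly impossible. In eight months 912 exceeds 800, the spread over practices is unknown, and section 2.6 gives both a target and an eight-month estimate without saying which prevails. A reader might infer that the target can never be met, and the article does not support that. An extreme concentration of patients in about a third of the practices, with almost no overflow past ten, would fit the totals. The objection stands as far as wording goes, but it does not rescue the plan. No gamma-type spread gives more than about 30 filled practices, and even the favourable case of 80 equal practices supplying everyone gives about 56.

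A reader might also infer that the trial would lose power. The figures show the reverse. Many small clusters have a lower design effect than 80 clusters of ten, and 80 × 10 itself gives 85%, above the planned 80%. The power figures are illustrative only, since section 2.11.1 applies a 40.1% yearly proportion to an outcome measured at six months.

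It is also fair to say that more practices means more work: physician consent, platform sign-up and training are required (sections 2.4, 2.6 and 3.1).

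**Conclusion.** The point holds as a conflict within the article and is wrong as written. The cluster size, the stopping rule and the recruitment period cannot in practice be carried out together. About 3.9 patients per practice are expected in eight months, where ten are required. Under assumed CVs of 0 to 2, about 1.5 to 30 practices fill, against 80 targeted and 72 needed by the sample size. Filling 80 takes about 17 to 18 months for CV 0 to 1, more than twice the eight planned, and longer above that. Separately, two of the three readings of the recruitment period miss 800 in total.

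The per-practice mean uses only the article's figures. The counts of filled practices rest on the assumed gamma-Poisson spread and a steady 114 a month. The damage shown is to timeline and execution, with an unplanned stopping decision left open. No loss of power is shown.

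**What to change.** - Stop on the total of 800 patients. Enrol every practice with an eligible consenting patient, and make ten a maximum per practice instead of a required size. A much lower maximum would bring the problem back: with five, the same model needs about 7.7 to 14.2 months to reach 800 for CV 0 to 1.
- Restate the design effect in section 2.11.1 with the expected mean and CV of cluster size. For CV 0 to 1 the mean is about 3.5 to 4.3, the size CV 0.5 to 0.7, and the design effect 1.17 to 1.27 in place of 1.45.
- Give one recruitment period, computed with the maximum of ten (about 7 to 7.8 months for CV 0 to 1, longer if patients are more concentrated), and align sections 2.6 and 2.12. Discharge counts by practice from the municipality's reports would replace the assumed CV.

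The number of patients is unchanged. The cost is protocol wording plus onboarding about 190 to 230 practices in place of 80, with the physician consent and training that go with it. Patients are already identified from city-wide reports and consultation is remote, but the added work is real and should be budgeted.

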### 2.7. Assignment of Interventions

#### 2.7.1. Allocation—Sequence Generation

Primary care practices from Rio will be stratified into four strata according to two factors, each having two levels: the family health strategy model running exclusively in the practice (presence or absence) and the Social Development Index (≤0.60 or >0.60). [24]. The research team has concluded that both factors are important determinants of the work process quality and patient outcomes, respectively [5,25,26].

We will randomise practices within each stratum after recruitment to control or intervention groups, using a computerised random number generator on a simple 1:1 allocation ratio to increase homogeneity between the groups. Once we randomise the practices, we will allocate the patients and apply the intervention of the physician or follow-up, depending on the group.

#### 2.7.2. Allocation—Concealment Mechanism 

The practices and patient allocation will be revealed only to researchers directly recruiting and assigning interventions (e.g., teleconsultation). The allocation will be concealed from the rest of the research team.

#### 2.7.3. Allocation—Implementation

An independent collaborator who does not participate in conducting the trial will receive the list of the practices to be stratified and randomised. After randomisation, they will send the recruiter an updated list containing allocation information. Based on the monthly report received from the Health Secretariat, the recruiter will allocate the patients in groups according to their registered practice. The researchers who are responsible for allocating and assigning interventions will not be involved in the intervention. Once one cluster reaches ten patients, the assignment for that cluster stops, in order to ensure equal cluster sizes.

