### 2.8. Blinding

Blinding of care providers is not possible, because those in the intervention group will receive teleconsultation support. The patients, outcome assessors, recruiters, data managers, and the data safety monitoring committee will be sought blinded. 

Two independent blinded statisticians will perform statistical analyses with the two intervention groups coded ‘A’ and ‘B’. The steering group will draw two blinded conclusions: one assuming ‘A’ is the experimental group and ‘B’ is the control group—and one assuming the opposite. Based on these two blinded conclusions, two abstracts will be written (and published as a supplement to the primary publication). When the blinding is broken, the ‘correct’ abstract will be chosen, and the conclusions in this abstract will not be revised.

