## Figures and Tables

**Figure 1 ijerph-20-05933-f001:**
[figure not shown]
Study workflow.

**Table 1 ijerph-20-05933-t001:** Participant Timeline.

Enrolment	T_−1_	T_0_	T_6_ (Close-Out)
General practice stratification and randomisation	X		
Patient eligibility screening using municipality data	X		
Invitation to participate (patient)	X		
Invitation to participate (physician)	X		
Informed consent (patient and physician)	X		
Patient allocation according to practice randomisation		X	
Intervention			
Intervention group		Teleconsultation support for the practice’s physicians (first contact and on demand)	
Control group		Usual care with follow-up of outcomes	
Assessments		T_0_	T_6_ (close-out)
1—Readmissions and Mortality (reports)			X
2—Days Alive Out of Hospital (DAOH)			X
3—Frequency of Serious Adverse Events			X
4—Symptoms Frequency and Severity		X	X
5—Quality of Life		X	X
6—Adherence to Prescribing Guidelines		X	X

**Table 2 ijerph-20-05933-t002:** Baseline Variables.

N	Variable	Field Type	Choices, Calculations, or Labels
Physician Variables—direct inquiry			
1	Name	Text	-
2	Social Identification Number (CPF)	Text	-
2	Completed years since graduation	Number	-
3	Specialisation	Option	Any/Family Medicine/Other
4	Completed years in primary care	Number	-
5	Completed years in the current practice	Number	-
6	Enrolled in a residency program	Options	No/Preceptor/1st year Resident/2nd year Resident/3rd year Resident/Program
Patient Variables—primary care electronic health record report			
1	Name	Text	-
2	Social identification number (CPF)	Text	-
3	National Health System identification number (CNS)	Text	-
4	Primary care practice	Text	
5	Gender	Options	Feminine/Masculine/Nonbinary
6	Race	Options	White/Black/Brown/Other
7	Birth date	Date	-
8	Weight (Kg)	Number	-
9	Height (cm)	Number	-
10	NYHA status	Options	1 to 4
11	Systolic blood pressure	Number	-
12	Diastolic blood pressure	Number	-
13	Heart rate	Number	-
14	Dyspnoea	Option	Yes/No
15	Leg Swelling	Option	Yes/No
16	Dizziness	Option	Yes/No
17	Fatigue	Option	Yes/No
18	Orthopnoea or paroxysmal nocturnal dyspnoea	Option	Yes/No
19	Syncope	Option	Yes/No
20	Typical chest pain	Option	Yes/No
21	Jugular vein distension	Option	Yes/No
22	Pulmonary rales	Option	Yes/No
23	ACE-I (names)	Option	ACE-I names
24	ACE-I dose	Number	-
25	ARB (names)	Option	ARB names
26	ARB dose	Number	-
27	Beta-blockers (names)	Option	BB Names
28	Beta-blockers dose	Number	-
29	Spironolactone	Option	Yes/No
30	Spironolactone dose	Number	-

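### The recruiter is given each practice's allocation while also inviting and consenting participants, yet recruiters are listed as blinded, and the order of randomisation and patient recruitment is left unresolved

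*Protocol article*

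**What the plan says.** Four places in the protocol article bear on who knows the arm, and when.

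- **Section 2.7.2 (concealment):** "The practices and patient allocation will be revealed only to researchers directly recruiting and assigning interventions".
- **Section 2.7.3 (implementation):** an independent collaborator randomises the practices. "After randomisation, they will send the recruiter an updated list containing allocation information". Then: "Based on the monthly report received from the Health Secretariat, the recruiter will allocate the patients in groups according to their registered practice". Accrual to a practice is capped: "Once one cluster reaches ten patients, the assignment for that cluster stops".
- **Section 2.8 (blinding):** "The patients, outcome assessors, recruiters, data managers, and the data safety monitoring committee will be sought blinded".
- **Section 2.7.1 (sequence generation):** "We will randomise practices within each stratum after recruitment to control or intervention groups".

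Section 2.6 describes the recruiter's work: identify the practice from the discharge report, invite the physician, and then "When the physician accepts, the recruiter invites the patient by telephone or in person". The recruiter also obtains both consent forms. Section 3.1 adds that the recruiter informs control-group physicians about the data collection, which is an arm-specific contact. In Table 1 the row "General practice stratification and randomisation" is marked at T-1, as are screening, both invitations and consent. Patient allocation is marked at T0.

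**The concern.** The role that controls entry to the trial is given the allocation in two sections and is declared blinded in a third. These statements cannot all stand.

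In a cluster trial with individual consent, randomising practices does not by itself make the patients comparable. Comparability also requires that patients enter without regard to the arm. If the recruiter knows the arm, or the physician does, then persistence in making contact, the physician's willingness to take part and the patient's willingness to consent may each differ between arms. The arms would then differ in case mix before any teleconsultation takes place. Section 2.11.2 adjusts the GEE models for the two stratification factors, the family health strategy model and the Social Development Index. Both describe practices, so they do not restore balance in patient-level risk.

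**Working it through.** **Step 1: does the recruiter hold the arm while still recruiting?** The document gives no figure here, so the sections are set side by side.

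| Question | Text | Answer |
|---|---|---|
| Who receives the allocation? | 2.7.2, 2.7.3 | The recruiter |
| Who invites and obtains consent? | 2.6 | The recruiter |
| Is accrual to a practice spread over time? | 2.7.3 (monthly report, cap of ten); 2.3.2 (practices join progressively) | Yes |
| Does the recruiter act differently by arm? | 3.1 | Yes, with control physicians |
| Is the recruiter blinded? | 2.8 | Intended to be |

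The last row conflicts with the first.

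**Step 2: does the wording in 2.7.1 remove the problem?** If all of a practice's patients had consented before the practice was randomised, the recruiter's later knowledge would be harmless. Section 2.6 expects 114 recruits per month.

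- Spread evenly over 236 practices: 114 / 236 = about 0.5 per practice per month.
- If all came from the 80 trial practices: 114 / 80 = about 1.4 per practice per month, so ten patients take 10 / 1.425 = about 7 months.

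On that reading the first patients would wait months for allocation, although eligibility is discharge within the past month (2.3.1). It also fits poorly with assigning monthly arrivals from a list that already carries the allocation. It is not excluded, however, because 2.7.1 does not say whose recruitment it means.

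**Step 3: how many patients are exposed?**

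- All patients consent before their practice is randomised: 0 of 800.
- Each practice is randomised straight after its first patient: 9 of 10 in each of 80 practices, 9 × 80 = 720.
- Practices are randomised before any patient is invited: 80 × 10 = 800.

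**Step 4: what could this do to the estimate? (illustration only)** All inputs are assumptions except the yearly rate of 40.1% in 2.11.1. Under a constant hazard that rate gives a six-month risk of 1 − (1 − 0.401)^0.5 = 22.6%. Assume that 25% of patients are high risk, with 45% event risk against 15.1% in the others: 0.25 × 0.45 + 0.75 × 0.151 = 22.6%. Assume no treatment effect, and 90% enrolment everywhere except for high-risk patients in control practices, where it is 70%.

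- High-risk share in control: (0.25 × 0.7) / (0.25 × 0.7 + 0.75 × 0.9) = 0.175 / 0.85 = 0.206.
- Control risk: 0.206 × 0.45 + 0.794 × 0.151 = 21.3%.
- Intervention risk: 22.6%.
- Apparent relative risk: 22.6 / 21.3 = 1.06. With the pattern reversed: 21.3 / 22.6 = 0.94.

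**Step 5: effect on error rates (illustration only).** With 80 clusters of 10 and ICC 0.05, the design effect is 1 + 9 × 0.05 = 1.45, and the effective size per arm is 400 / 1.45 = 276. The reversed pattern in step 4 is a 1.3-point shift. Its standard error is √[(0.226 × 0.774 + 0.213 × 0.787) / 276] = 0.035. The chance of a falsely significant benefit is P(Z > 1.96 − 0.0132 / 0.0352) = P(Z > 1.585) = about 6%, against a nominal 2.5% in that direction. By the same formula at a control risk of 40.1%, assumed shifts of 2, 4 and 6 points give about 7%, 16% and 31%.

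The planned sample size is not affected by this point.

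**The case against.** Several things can fairly be said for the plan.

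- **Identification is protected.** Candidates come from a municipal discharge report selected by ICD-10 code, and the team expects to invite every discharged patient (2.6). Neither recruiter nor practice chooses whom to list. This stands, and it narrows the concern to acceptance, consent and persistence.
- **The blinding statement is an intention.** Section 2.8 says that blinding will be sought. The conflict is softer for that, but a role that is sent the list cannot be sought blinded to it.
- **Allocating researchers take no part in the intervention (2.7.3).** This separates them from delivering teleconsultation. It does not separate them from inviting and consenting.
- **The illustration is modest.** It assumes 30% non-enrolment of high-risk patients in one arm, where 2.6 expects 10% refusal overall, and it still moves the relative risk by only about 6%, against a planned 30% effect. This stands, and the illustration does not carry the case.

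A reader might also infer three stronger things that the document does not support.

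- *Table 1 shows randomisation ahead of invitation and consent.* They share the T-1 column, and only the row order suggests a sequence.
- *The recruiter also collects the patients' baseline outcome data.* Section 3.1 assigns baseline physician data to recruiters, while interviewers apply the EQ-5D-5L and SSQ-HF. It does not say that these are the same people.
- *720 of the 800 patients are approached with the arm known.* That is one scenario within the range of 0 to 800.

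**Conclusion.** The point holds as an internal contradiction with a consequence for conduct. Sections 2.7.2 and 2.7.3 give the allocation to the person who invites and consents, and section 2.8 counts that person among the blinded. The order of randomisation and patient recruitment cannot be settled from 2.7.1 and Table 1. The number of patients exposed therefore lies anywhere from 0 to 800, although monthly assignment from an allocated list makes 0 the least natural reading.

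The conclusion rests on the text, not on the calculation. The relative risk of 0.94 to 1.06 and the error rates depend on assumed enrolment patterns and show only that plausible selectivity would matter. They do not show that bias will occur, or in which direction. The plan needs correction all the same, because imbalance created at patient entry cannot be repaired by the planned adjusted GEE.

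**What to change.** Reconcile sections 2.7.1 to 2.7.3, 2.8, 3.1 and Table 1 to one sequence:

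1. The physician agrees and the practice is stratified.
2. The patient consents, and baseline data, including EQ-5D-5L and SSQ-HF, are completed and locked in REDCap.
3. Only then does the independent collaborator, who keeps the list, release the arm, and only to the staff who activate teleconsultation.

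Recruiters use one script for both arms and do not see the list. The arm-specific conversation with control physicians moves to the activating staff. Where feasible, consent the patients already identified in a practice before that practice's arm is released.

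This does not restore full concealment. Once its first patient is activated, a practice knows its arm, and a recruiter who contacts the physician about the next patient may learn it. The article should say so, correct the blinding statement accordingly, and commit to reporting numbers screened, invited and consented, with baseline characteristics, by arm.

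The cost is a protocol amendment, a change in access rights and a short delay between consent and activation. The independent collaborator (2.7.3) and role-restricted REDCap access (2.10) are already in place.
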